## Abstract

**Background:**

A significant proportion of patients with chronic tinnitus report clinical levels of sleep disturbance (insomnia). Despite the significant health and functioning implications of this, no rigorous trials have investigated treatments that target tinnitus-related insomnia. This is the first randomised controlled trial evaluating Cognitive Behavioural Therapy for insomnia (CBTi) in tinnitus compared with other psychological treatments.

**Methods/design:**

The study will test the efficacy of group CBTi as a treatment for tinnitus-related insomnia in a single-centre randomised controlled trial. Participants will be 102 patients with chronic, clinically significant tinnitus and insomnia in the absence of organic sleep disorders. Participants will be randomised to one of three intervention arms: six sessions of CBTi or six sessions of sleep support group or two sessions of audiologically based care. The primary outcomes will be changes in sleep as measured on the Insomnia Severity Index and key outcomes on a 2-week sleep diary (sleep efficiency and total sleep time). Outcomes will be collected 3, 10, 14 and 34 weeks post-randomisation. Secondary measures include sleep quality, sleep beliefs, tinnitus severity, psychological distress and quality of life. A sub-sample of participants will provide two weeks of actigraphy data at the same time points. Data on satisfaction and treatment experience will be collected at 10 and 34 weeks post-randomisation from all participants.

**Discussion:**

Findings from the study will be submitted to a peer-reviewed journal. It is anticipated that findings may inform future clinical practice in the treatment of tinnitus-related insomnia.

**Trial registration:**

ClinicalTrials.gov, NCT03386123. Retrospectively registered on 29 December 2017.

## Background

Tinnitus represents a significant population burden, with distressing tinnitus experiences reported by 1–2% of the population [1]. When tinnitus is bothersome, it is associated with many challenges, including difficulties with concentration, auditory perception, emotional distress and sleep. One of the most common problems is sleep disturbance, reported by 50–70% of people with tinnitus [2]. Despite being so widespread, insomnia in tinnitus is poorly defined and understood [3]. A recent review indicated prevalence rates of insomnia in tinnitus as varying from 10% to 80%, with most studies reporting rates above 40% [4]. However, diverse assessments have been used to define ‘insomnia’, and only one used full diagnostic criteria (reporting a rate of 27%).

Clearly, sleep disturbance is not inevitable in severe tinnitus, and many patients sleep well despite disabling tinnitus. Some reports, however, have suggested that tinnitus severity is associated with poorer sleep [5, 6] and lower quality of life. Yet, intervention studies to investigate whether insomnia-related tinnitus could benefit from more specialist intervention remain to be done.

This is of interest, given that there is evidence of similarity between tinnitus-related insomnia and primary insomnia. Cross-sectional studies comparing tinnitus patients with healthy control subjects using polysomnography have found that tinnitus is associated with increased sleep onset latency (SOL), as well as waking after sleep onset, decreased sleep efficiency (SE) and total sleep time (TST) [7]. Studies comparing patients with tinnitus-related insomnia with patients reporting primary insomnia show little significant difference between the groups on either objective measures of brain activity or subjective measures from sleep diaries and questionnaires, including daytime fatigue, mood and concentration [7, 8].

Stressful life events, associated autonomic hyperarousal, changes in serotonin and depressed mood have been identified as precipitants and maintaining factors in both tinnitus and insomnia [9, 10]. The cognitive models of tinnitus [11] and insomnia [12] share significant similarities, including stress arousal, negative thoughts about the symptoms, hypervigilance and monitoring for threatening symptoms, and safety-seeking behaviours. In patients with tinnitus, subjective measures of sleep quality and insomnia-related fears are elevated compared with healthy control subjects [13], suggesting typical insomnia-related cognitive behavioural processes (although direct comparisons with patients with insomnia are yet to be tested). Patients tend to attribute sleep problems to the noise of tinnitus. This attribution is difficult to validate, however, because both symptoms can be triggered by stress and illness, and tinnitus can cause stress and worry, further compounding insomnia. Overall, such findings suggest that cognitive behavioural treatments that can target primary insomnia could also apply to tinnitus-related insomnia [8].

This suggestion is yet to be tested because no clinical trials have targeted tinnitus-related insomnia. Sleep problems are not reliably measured or reported, and clinical insomnia is not identified within research samples. Psychological interventions for tinnitus are effective in terms of improving distress and quality of life, with evidence for cognitive behavioural therapy (CBT), mindfulness-based cognitive therapy and acceptance and commitment therapy [14–16], but none specifically target sleep. A few studies have found that sleep improved as part of general biofeedback and CBT interventions [17–19]. However, most include participants with non-clinical insomnia or have used poor-quality outcome measures [2, 20, 21].

Standard audiology-based care (ABC) for tinnitus-related insomnia involves one or two sessions with an audiologist and provides a mix of psychoeducation, advice to use external sound to partially mask tinnitus and advice about sleep hygiene (good habits regarding sleep/bedroom). A bedside sound generator is often provided, offering a choice of soothing sounds (e.g., wind, rain, waves, white noise). Various supporting literature may be given, such as information leaflets from the national tinnitus charity, the British Tinnitus Association. As described, reviews of tinnitus management rarely identify sleep as an outcome; as a result, there is no clear evidence regarding whether this ‘standard’ care for tinnitus provided by audiology services is in fact effective in managing insomnia. Thus the tinnitus literature offers minimal information about the nature and management of tinnitus-related insomnia, and studies are urgently required to improve understanding of this debilitating condition.

There are good reasons to suppose that specialised cognitive behavioural therapy for insomnia (CBTi) might help in this context. CBTi is the treatment of choice for primary insomnia, showing medium to large effect sizes [22, 23]. More importantly, it is also an effective treatment for insomnia secondary to other conditions such as pain, depression and cancer [23–29]. Tang and colleagues [26, 29] argued that secondary insomnia must be targeted directly using an approach such as CBTi and that sleep problems will not resolve alone, even if pain is successfully treated. They also noted that sleep deprivation can reduce pain tolerance. Because tinnitus shares some similarities with chronic pain [30], it is possible that similar processes apply to tinnitus-related insomnia. In chronic pain, the intervention for insomnia assumes that, although pain may trigger insomnia, the sleep problems are maintained and exacerbated by the development of behavioural habits around sleep. It is likely that this is also the case in chronic tinnitus. The reported benefits of CBTi in chronic pain settings led us to believe that it might also benefit patients with tinnitus-related insomnia. This is as yet not properly tested, but a recent clinical evaluation of group CBTi for tinnitus-related insomnia demonstrated significant improvements in sleep, tinnitus and distress [31].

### Defining insomnia

The insomnia literature offers the most useful definitions [24, 29], measures [24, 32, 33] and criteria for improvement [32, 34, 35], so far absent from the tinnitus literature. This will guide the definitions, measures and inclusion criteria used in this study.

### Rationale

Because tinnitus-related insomnia is common and associated with severe distress, it is important to test the most effective treatment. As yet, evidence for standard audiologically based care (ABC) for tinnitus-related insomnia does not exist, and whilst evidence for CBTi in a variety of health conditions is strong, it has not been tested in tinnitus. Robust testing will require a randomised controlled design. Because treatment intensity is different (CBTi involves six sessions, ABC rarely more than two) a third treatment arm involving six sessions of a supportive sleep group (SSG) will balance the CBTi contact time. Because tinnitus and insomnia are chronic conditions, a follow-up period of at least 6 months is required.

### Research aims and hypotheses

#### Primary objective

The primary objective is to assess the relative efficacy of CBTi compared with ABC for tinnitus-related insomnia from pre- to post-treatment and at 1- and 6-month follow-up time points.

Hypothesis 1A: CBTi will lead to a significantly greater reduction in insomnia than ABC from pre- to post-treatment and at follow-up, as indicated by mean changes on the Insomnia Severity Index (ISI).

Hypothesis 1B: CBTi will lead to a significantly greater reduction in insomnia than ABC from pre- to post-treatment and at follow-up, as indicated by mean changes on SE and TST, measured by a 2-week daily sleep diary.

#### Secondary objectives

Hypothesis 2A: A greater proportion of patients receiving CBTi will show a reliable clinical change in insomnia (> 6-point reduction on the ISI) compared with ABC and SSG.

Hypothesis 2B: CBTi will lead to a significantly greater reduction in insomnia than SSG from pre- to post-treatment and at follow-up, as indicated by mean changes on the ISI, SE and TST.

Hypothesis 2C: ABC will lead to a significantly greater reduction in insomnia than SSG from pre- to post-treatment and at follow-up, as indicated by mean changes on the ISI, SE and TST.

Hypothesis 2D: Compared with both ABC and SSG, CBTi will lead to significantly greater mean changes in measures of tinnitus-related distress, tinnitus catastrophising, psychological distress, anxiety, depression, quality of life and functioning from pre- to post-treatment and at follow-up.

Hypothesis 2E: A greater proportion of patients receiving CBTi will show a reliable change on the measure of tinnitus distress (> 11 points on the Tinnitus Questionnaire) compared with ABC and SSG.

Hypothesis 2F: Participants receiving CBTi will show a greater reduction in dysfunctional beliefs about sleep than those receiving ABC or SSG, and this reduction will be associated with greater improvements in insomnia.

Hypothesis 2G: There will be no significant differences between the three groups in terms of changes in subjective tinnitus loudness after treatment.

The study will monitor safety (incidence of adverse reactions), acceptability and patient satisfaction with each treatment. Adverse events will be solicited in the feedback form and may arise spontaneously. If reported, adverse events will be recorded and included in the final report. Participants will be offered psychological support outside of the trial, or the general practitioner (GP) will be contacted as appropriate.

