**Audiology-based care (ABC):** ABC will be based on the best care currently available to patients with tinnitus and insomnia in the United Kingdom. There is no set standard, so this group has been designed to capture what is currently seen as best advice for people with tinnitus and insomnia. The group has been designed to be as effective as possible, because the intervention is being delivered by two clinical psychologists experienced in working in an audiological setting and in a supportive group setting. Intervention includes information and psychoeducation about tinnitus, sleep and relaxation. A bedside sound generator will be on loan for 3 months. Therapeutic contact is limited to two sessions 8 weeks apart. Supporting literature (leaflets from the British Tinnitus Association on sleep, tinnitus and relaxation) will be provided.**Cognitive behavioural therapy for insomnia (CBTi):** CBTi will follow the UK standard treatment of primary insomnia, adapted for tinnitus. This multi-component treatment includes time-in-bed restriction, stimulus control, sleep hygiene, relaxation, paradoxical intention, cognitive restructuring, behavioural experiments and behavioural activity change. Additional discussions will focus on information, psychoeducation and advice about tinnitus management. Six sessions will occur over 8 weeks (four weekly sessions followed by two fortnightly sessions).**Sleep support group (SSG):** This supportive intervention focuses on the benefits of clinical contact and a supportive milieu. It is an active condition controlling for the non-specific benefits of supportive group therapy. Sleep and tinnitus will be discussed from a personal perspective, focusing on personal stories and how participants cope. Participants will be encouraged to support each other. No expert audiological or psychological information will be provided, but therapists will facilitate discussion and adaptive group dynamics. Six sessions will follow the pattern of CBTi (four weekly sessions followed by two fortnightly sessions).

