### Secondary outcome analysis

As for the primary analysis, a linear mixed model will be used to investigate differences in outcome between the three groups at additional time points (1-month and 6-month follow-up) and on all secondary outcome measures described above. In addition, correlational analyses will be used as a quality control to check for the level of association between actigraphy and sleep diary data, including TST, TWT, SOL and SE.

Regression analyses will be conducted to assess whether changes in the primary outcome measure (ISI, TST, SE) are associated with changes in sleep beliefs (DBAS-16) score.

Satisfaction will be assessed via a single three-group analysis of variance on treatment usefulness and relevance. Written responses will be analysed using thematic analysis. Treatment adherence will be assessed on the basis of attendance rates. Categorical outcomes, including adverse events and non-adherence, will be recorded, reported and compared with Fisher’s exact test.

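### Adverse events from form and spontaneous reports are compared between arms without separation by source, so unequal contact can bias the contrasts with ABC

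*Protocol article*

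**What the plan says.** Under Secondary objectives, the protocol article undertakes to monitor safety with each treatment and names two routes by which events are found: "Adverse events will be solicited in the feedback form and may arise spontaneously". It adds: "If reported, adverse events will be recorded and included in the final report". Under Secondary outcome analysis it commits to a between-arm test: "Categorical outcomes, including adverse events and non-adherence, will be recorded, reported and compared with Fisher’s exact test". Neither section separates the routes or limits the test to one of them.

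Contact differs by arm (Intervention section). For ABC, "Therapeutic contact is limited to two sessions 8 weeks apart". For CBTi, "Six sessions will occur over 8 weeks (four weekly sessions followed by two fortnightly sessions". For SSG, "Six sessions will follow the pattern of CBTi (four weekly sessions followed by two fortnightly sessions". The same section mentions follow-up sessions besides the treatment sessions but does not give their number by arm.

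The abstract states: "Data on satisfaction and treatment experience will be collected at 10 and 34 weeks post-randomisation from all participants". This appears to be the feedback form that solicits adverse events, although the article does not say so outright.

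**The concern.** The two routes do not have the same reach. A form completed at 10 and 34 weeks by everyone asks each arm equally often. A spontaneous report needs an occasion, and the main occasion is a session with the therapists. CBTi and SSG offer three times as many treatment sessions as ABC, so the recorded count reflects the visit schedule as well as harm.

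The distortion runs in one direction, against the two longer arms. It touches CBTi against ABC, which is also the contrast of the primary objective, as well as SSG against ABC and any three-arm test. A reader of the final report could take a difference produced by contact for a difference in harm. Separating the sources at analysis is possible only if the source of each event was recorded.

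**Working it through.** The article gives no adverse event rate and no power for safety, so there is no figure of its own to reproduce. The check asks how large a difference unequal contact can produce when true harm is equal.

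**Inputs from the article**
- Treatment sessions: 6 (CBTi, SSG) and 2 (ABC), ratio 6/2 = 3.
- Sample size: 34 per arm.
- Form: same schedule in all arms, if it is the 10- and 34-week feedback.

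**Assumptions (not in the article)**
- True risk p of an event, the same in both arms: 10% to 50%.
- Probability s that the form captures the event: 30% to 50%, with 90% as a contrast.
- Probability q that a patient volunteers the event at any one session: 10% to 20%.
- Follow-up sessions: either ignored (6 v 2), or one at 14 and one at 34 weeks in every arm, giving 6 + 2 = 8 v 2 + 2 = 4 contacts, ratio 2.

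**Formula.** With k contacts, an event is recorded with probability 1 − (1 − s)(1 − q)^k. Recorded incidence is p times this. The spurious risk ratio is the ratio of the two capture probabilities, so p cancels.

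**Example, s = 0.3, q = 0.2**
- k = 6: 1 − 0.7 × 0.8^6 = 1 − 0.7 × 0.262 = 0.816
- k = 2: 1 − 0.7 × 0.8^2 = 1 − 0.7 × 0.640 = 0.552
- Ratio: 0.816/0.552 = 1.48
- k = 8 and k = 4: 0.883 and 0.713, ratio 1.24

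**Results**, using the exact rejection probability of the two-sided Fisher test at 5% for one two-arm contrast with 34 per arm:

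| p | s | q | 6 v 2: recorded | Ratio | Falsely significant | 8 v 4: recorded | Ratio | Falsely significant |
|---|---|---|---|---|---|---|---|---|
| 10% | 30% | 20% | 8.2% v 5.5% | 1.48 | about 1% | 8.8% v 7.1% | 1.24 | about 1% |
| 20% | 50% | 10% | 14.7% v 11.9% | 1.23 | 2.5% | 15.7% v 13.4% | 1.17 | about 2.5% |
| 30% | 50% | 20% | 26.1% v 20.4% | 1.28 | 4.8% | 27.5% v 23.9% | 1.15 | 3.4% |
| 30% | 30% | 20% | 24.5% v 16.6% | 1.48 | 7.5% | 26.5% v 21.4% | 1.24 | 4.3% |
| 50% | 30% | 20% | 40.8% v 27.6% | 1.48 | 15.1% | 44.1% v 35.7% | 1.24 | 7.5% |
| 30% | 90% | 20% | 29.2% v 28.1% | 1.04 | 2.7% | 29.5% v 28.8% | 1.03 | 2.7% |

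For comparison, with equal capture the test rejects in at most about 3% of trials at this sample size. With about 31 analysed per arm (10% loss), the 15.1% becomes 13.2%.

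**After the fix.** If only form-solicited events are tested, capture is s in every arm, the expected ratio is 1.00 and the false-positive rate stays at or below about 3%.

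The model is simple. It treats every session as an equal chance to report and ignores clustering within treatment groups.

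**The case against.** Collecting solicited and spontaneous events together is ordinary practice. The form puts the same question to all arms, so most of the ascertainment may be balanced. SSG was added to match CBTi on contact time, which leaves one safety comparison of CBTi free of this problem. The article does not say that the two sources are summed, and tabulation by source is a detail that a full protocol or analysis plan might hold. Taking spontaneous events out of the comparison could also hide harms that the form misses.

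Much of this stands. It confines the problem to contrasts with ABC and limits its size. It does not remove the problem: as written, the test covers adverse events with no restriction by source, and one source depends on the schedule.

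Three stronger readings are tempting and are not supported:
- A reader might infer a very high false-positive rate. If spontaneous reporting were the only route, with 5% or 10% of patients volunteering an event at each session and no follow-up sessions, Fisher's test would be significant in about 32% or 61% of trials. That model leaves out the form, which the article names as a source, and the follow-up sessions.
- A reader might infer that ABC looks safer because nobody asked. If the form is the 10- and 34-week feedback, every arm is asked.
- A reader might infer that the safety objective cannot be answered. The objective is to monitor incidence with each treatment, no safety hypothesis is attached, and CBTi against SSG remains interpretable on this point.

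**Conclusion.** The point holds in a limited form. The planned comparison can show more adverse events in CBTi and SSG than in ABC when true harm is equal, because spontaneous reporting follows contact. Over the assumed ranges with the form included, the spurious risk ratio is about 1.15 to 1.5. False significance occurs in about 1% to 15% of trials with 6 v 2 sessions, and in about 1% to 7.5% with 8 v 4 contacts. It clearly exceeds 5% only when events are common and the form captures few of them. With rare events a falsely significant test is unlikely, and the harm is mainly a distorted reported incidence. With near-complete form capture there is little bias.

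All rates are assumptions, as is the reading that the adverse event question sits on the 10- and 34-week feedback form. The size is moderate and concerns a secondary objective. The correction is cheap and worth making.

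**What to change.** - Record for each adverse event whether it came from the form or from a spontaneous report.
- Base the between-arm test on events solicited by the same form at the same times in all arms, and state those times.
- List spontaneous reports separately by arm, with the number of contacts in each arm, outside the test.

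The cost is one field per event and a few lines in the analysis plan. No extra assessment is needed. Recruitment was complete when the article was proofed, so the source of events already recorded may have to be taken from existing records. The small downside is that spontaneous events are described and not tested. They must still be reported in full, so that harms the form misses remain visible.

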## Methods/design

This randomised controlled trial will assess the effectiveness of CBTi for tinnitus-related insomnia using three independent groups and repeated measures. All three groups will be assessed at four time points post-randomisation: 3 weeks (pre-treatment), 10 weeks (post-treatment), 14 weeks (1-month follow-up) and 34 weeks (6-month follow-up). All interventions will take place within a single centre, a UK specialist ear, nose and throat hospital.

### Participants

Participants will be adults with chronic distressing tinnitus and related insomnia. They will be randomly allocated to receive CBTi, ABC or SSG.

### Inclusion and exclusion criteria

Participants are eligible if they report:
Presence of insomnia for a minimum of 3 months (scoring 15 or more on the ISI);At least moderately distressing tinnitus for at least 6 months (scoring 8 or more on the Mini-Tinnitus Questionnaire [Mini-TQ]);Sleep problems directly related to tinnitus;Absence of organic sleep disorders (as assessed by a sleep disorder screening questionnaire);Tinnitus has been fully assessed by a doctor/audiology specialist;Aged between 18 and 70 years;English proficiency and hearing level allow for participation in a group; andWilling and able to provide informed consent to take part in a sleep-focused group treatment.

Participants will be excluded if they report:
Current, comorbid, severe physical or mental illness;Active risk of harm to self or others;Current substance dependence;Current/planned pregnancy or breastfeeding; andMedical investigations into sleep or tinnitus incomplete.

Participants taking hypnotic or psychotropic medication at the point of consent will be asked to keep this stable for the duration of the trial and not to engage in additional psychotherapy.

